### Treatment integrity

Treatment fidelity is ensured via standardized and manualized treatment and study procedures, ongoing supervision (i.e., study therapists attend 2 hours of supervision every month and yoga teachers attend 1 hour-long supervision meeting every month) and ongoing therapist/yoga instructor adherence ratings. Fidelity raters rate a random 10% of all recorded sessions to ensure study procedure adherence. Raters use a structured checklist to document fidelity to the respective manuals.

### Measures

Unless otherwise noted, participants complete all measures via self-report in REDCap. (See Fig 2).

**Fig 2 pone.0315506.g002:**
[figure not shown]
Schedule of enrollment, interventions, and assessments.

#### Primary outcome measure

The primary outcome, depression symptom severity, is assessed using the Patient Health Questionnaire-9 (PHQ-9), which is a 9-item self-report questionnaire [52, 70]. A PHQ-9 score ≥10 has a sensitivity of 88% and a specificity of 88% for major depression. PHQ-9 scores range from 0–27; scores of 5, 10, 15, and 20 represented mild, moderate, moderately severe, and severe depression, respectively [52].

#### Secondary outcome measures

Well-being is assessed using The World Health Organization-5 Well-Being Index (WHO-5) [71, 72], a 5-item self-report questionnaire with positively worded statements related to positive mood, vitality, and general interest over the prior two weeks. The WHO-5 is reliable, has shown strong construct validity as a measure of general well-being, and is sensitive to change [71, 72]. Anxiety and sleep disturbance are assessed using the PROMIS-29 [73], which has seven health domains (physical function, fatigue, pain interference, depression, anxiety, ability to participate in social roles and activities, sleep disturbance). The PROMIS-29 has demonstrated good psychometric properties [73].

#### Exploratory outcome measures

Physical function, fatigue, pain interference, depression, and ability to participate in social roles and activities PROMIS-29 scales are exploratory outcomes. Other exploratory outcomes include substance use, irritability, and treatment utilization. The Tobacco, Alcohol, Prescription medication, and illicit Substance use screening Tool Adapted (TAPS-1) [74] is a 4-item screener adapted from the National Institute on Drug Use and used to measure frequency of tobacco, alcohol, prescription medication, and illicit substances (e.g., cocaine, marijuana, methamphetamine) use. The PROMIS-Anger is a 5-item self-report scale used to measure the exploratory outcome of irritability [75]. A final exploratory outcome will be the number of days of psychiatric inpatient and day hospital treatment in the past 12 weeks, assessed via a self-report questionnaire. These data will be used to examine differences in service usage between the two comparator groups.

#### Safety assessments

The Columbia Suicide Severity Rating Scale, Screener/ Recent–Self-Report (CSSRS-SR) is used to assess suicide-related thoughts and behaviors [76]. The Systematic Assessment for Treatment Emergent Effects (SAFTEE) [77] is widely used in both clinical and research contexts to assess new adverse events over the course of treatment. We will use a modified, self-report version (tailored for the study interventions) that we have successfully used to track adverse events in previous studies [78, 79].

#### Heterogeneity of treatment effect (HTE) variables

HTE variables are used in statistical analyses to understand whether certain subgroup of individuals experience increased benefit from one intervention vs. another. As such, these assessments are administered at baseline only. Participants’ preference for the two treatments, yoga or psychotherapy, is assessed using a single item: “If you had a choice, which program would you prefer to be in?”. Responses range from 1 to 5, where lower scores indicate a stronger preference for BA psychotherapy, and higher scores indicate a stronger preference for yoga [80–82]. The Credibility Expectancy Questionnaire (CEQ) [83] is used to measure treatment expectancy and rationale credibility. It has demonstrated high internal consistency and good test–retest reliability [83]. Finally, the Multidimensional Assessment of Interoceptive Awareness-2 (MAIA-2) [84] assesses the degree to which one experiences one’s body as safe and trustworthy as this may impact one’s comfort and ability to engage in a movement program, such as a YI. The MAIA-2 has demonstrated good psychometric properties [84]. We will use the Body Listening subscale (3 items) and the Trusting subscale (3 items) based on previous research [85–87] and to minimize participant burden. We will also examine the impact of depression severity using the PHQ-9.

#### Sample characteristics

A DSM-5 diagnosis of major depressive disorder or bipolar disorder over the past year is measured by participant responses to the self-report mania/hypomania and major depression sections of the Composite International Diagnostic Interview Screening Scales (CIDI-SC) [74]. The Altman Self-rating Mania Scale (ASRM) [53] is used to assess current manic symptoms. Participants are also asked at baseline to self-report on demographic variables.

#### Treatment utilization

We assess medications prescribed at weeks 0 and 24. Yoga class attendance (including any non-study classes) and amount of personal yoga practice outside of class is assessed by the Yoga Practice Questionnaire [70]. Staff also take attendance at study yoga classes; number of BA sessions completed is tracked by therapist report. For those in the BA condition, the extent to which participants practice the skills they learn in BA outside of therapy sessions is measured by the BA homework record [88], which is completed by the BA therapists and assesses how many activities are scheduled and the extent to which the participant completed each activity.

#### Qualitative intervention feedback

Participants are asked to respond to three open-ended questions about their intervention experience: “How did you use what you learned in the yoga/BA program in your daily life?”, “What got in the way of you using skills from the yoga/BA program in your daily life?”, and “How could we have made this yoga/BA program more helpful to you?” These data will be used inform future trials.

### Statistical analysis

We designed the study to determine the noninferiority of YI versus BA with a margin of 2 points on the PHQ-9 at week 24 (primary outcome). This margin was chosen as its magnitude was below established thresholds of a clinically meaningful difference on the PHQ-9 (which range from 3–5 in the literature) [52]. We arrived at this conclusion based on a few lines of reasoning. One strategy for determining a non-inferiority margin is by calculating it as one half of the mean control effect size from previous trials. A previous study of behavioral activation (BA) vs. cognitive behavioral therapy (CBT) calculated the non-inferiority margin to be 1.9 PHQ-9 points, based on a meta-analysis of previous BA trials that estimated a difference between BA and control groups of 3.8 PHQ-9 points [89]. Another study also choose a margin of 2 based on three pieces of evidence: a) a change of 2 on the PHQ-9 would correspond to a small effect size (assuming a standard deviation of 6.9), which is typically seen to be of limited clinical value; b) 2 points on the PHQ-9 represents an effect size of less than one half the expected difference between treatment and usual care; and c) psychologists using the PHQ-9 in clinical practice did not see a change of less than 2 points on the PHQ-9 to be a change that was clinically important [90]. A margin of 2 points on the PHQ-9 has also been used in prior noninferiority trials of depression treatments [91–96]. We include the non-inferiority margins for secondary outcomes in Table 3.

**Table 3 pone.0315506.t003:** Non-inferiority margins and power estimates for primary and secondary outcomes.

Outcome Type	Description	Measure	Non- inferiority Margin [Supporting Citations]	Anticipated Standard Deviation
Primary	Depressive symptoms	PHQ-9^a^	2 points^d^	7 points
Secondary	Well-being	WHO-5^b^	1.5 points [95, 109]	5 points
Secondary	Anxiety	PROMIS-29^c^	3 points [92–94]	10 points
Secondary	Sleep Disturbance	PROMIS-29^c^	3 points [92–94]	10 points

^a^ Range of possible scores = 0–27.

^b^ Range of possible scores = 0–25.

^c^ Converted to t-scores, i.e., with a mean = 50 and SD = 10.

^d^ See text for supporting citations.

Assuming an actual mean difference of zero, a standard deviation of 7 in both arms [97, 98], and a 25% dropout rate by week 2 [33], a sample size of 518 (259 participants per arm) provides 80% power to establish the noninferiority of the YI versus BA based on a one-sided 2.5% significance level t-test against the margin of -2 points.

All statistical reporting will adhere to guidelines in the CONSORT extension for noninferiority trials [99]. The primary outcome is patient-reported depression symptom severity (PHQ-9) at week 24. The difference in the mean scores at week 24 will be estimated using a linear mixed effects model with random participant intercepts and slopes and fixed effects for intervention arm, study site, time in weeks, and intervention-by-time interaction. Natural cubic splines or categorical time regression terms will be used if mean trajectories are nonlinear. The non-inferiority of the YI will be established based on a one-sided 2.5% significance level test of the estimated difference in means against the prespecified margin of 2 points. We will also report corresponding model-based estimates with 95% confidence intervals (CIs).

Secondary outcomes including well-being (WHO-5), anxiety, and sleep (PROMIS-29) will be analyzed similarly using linear mixed models, one-sided noninferiority tests against the prespecified margins, and model-based estimates with CIs. A multiplicity correction will be used to interpret secondary outcome results to maintain an overall family-wise error rate of 5%. Exploratory outcomes will be analyzed using linear mixed models or other appropriate longitudinal regression models (e.g., quasi-poisson generalized estimating equation model for number of days of psychiatric inpatient treatment); exploratory results will emphasize model-based estimates and CIs.

To examine potential heterogeneity of treatment effect (HTE), we will include participant-level baseline variables as moderators in the primary outcome model for PHQ-9 described above. Prespecified moderators include intervention preference, perceived intervention credibility, trust in one’s body, and depression severity. For each potential moderator, the linear mixed effects model for the PHQ-9 described above will be expanded to include an additional fixed effect for each moderator, a three-way moderator-by-intervention-by-time term, and all lower-order two-way interactions. HTE will be formally evaluated using a likelihood ratio test of the three-way interaction term, a term representing the estimated differential intervention effect across levels of the moderator. Model-based estimates, 95% CIs, and p-values will be presented descriptively using tables and figures (e.g., a forest plot). Additionally, we plan to explore the role of demographics, clinical diagnoses, and treatment history as potential moderators. We will follow a similar HTE analytic strategy for these post hoc exploratory moderators and report model-based estimates with 95% CIs.

Our primary linear mixed models incorporate all available longitudinal data from participants including those that drop out of the study prior to week 24. Sensitivity analyses will be conducted by further adjusting regression models (and, thus, model-based estimates and CIs) for any baseline imbalances between intervention groups or any variables known or suspected to be associated with dropout or missingness. We will also provide thorough summaries of reasons for missingness, proportions of missing data, and differences in the characteristics of patients with and without missing data.

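### The primary week-24 comparison is not adjusted for baseline PHQ-9: a valid choice, but one that loses precision for nothing and leaves the estimate exposed to chance baseline imbalance

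*Protocol article*

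**What the plan says.** The Statistical analysis section of the protocol article lists the terms of the primary model: "random participant intercepts and slopes and fixed effects for intervention arm, study site, time in weeks, and intervention-by-time interaction". The target is the level at week 24, not a change from baseline. Non-inferiority is decided "based on a one-sided 2.5% significance level test of the estimated difference in means against the prespecified margin of 2 points". If trajectories are not linear, time may be modelled by splines or categories; the arm term remains.

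Later in the same section, "Sensitivity analyses will be conducted by further adjusting regression models (and, thus, model-based estimates and CIs) for any baseline imbalances between intervention groups". That sentence goes on to a second group of covariates: variables known or suspected to be linked to dropout or missing data. Depression severity is also one of the prespecified moderators, in separate models that extend the primary one. Secondary outcomes are to be analysed in the same way as the primary.

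Randomization is stratified by site only (Study procedures). PHQ-9 at entry must lie between 10 and 20 (Table 2), so every randomized participant has a baseline score.

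**The concern.** A mixed model does not adjust for baseline merely because it is longitudinal. There are two cases, and the article does not say which applies.

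- If week 0 is among the outcomes, the free arm term gives each arm its own baseline mean. The week-24 contrast then carries any chance difference at baseline.
- If week 0 is not among the outcomes, the baseline score is not used at all.

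Either way, the most obvious prognostic variable in the trial does not inform the primary test. The decision rests on where a confidence limit falls against a 2-point margin, so a wider interval than necessary, or an estimate shifted by baseline luck, matters directly. A sensitivity analysis does not govern that decision. To the extent that its covariates are chosen by observed imbalance, they are not fixed in advance.

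**Working it through.** **1. The plan's own figure.** Inputs from the Statistical analysis section: "Assuming an actual mean difference of zero, a standard deviation of 7 in both arms", margin 2, one-sided 2.5%, and "a 25% dropout rate by week 2", applied here as the loss at the week-24 analysis.

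- Normal approximation: n = 2 × 7² × (1.960 + 0.842)² / 2² = 192.3, so 193 per arm.
- Exact t-test: 194 per arm, power 80.1%.
- With 25% loss: 194 / 0.75 = 258.7, so 259 per arm and 518 in total.

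This matches "a sample size of 518 (259 participants per arm) provides 80% power". The size therefore rests on the raw SD of 7, with no credit for baseline, and agrees with an unadjusted analysis.

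**2. What adjustment would add.** Let ρ be the correlation between baseline and week-24 PHQ-9. It is not in the article, so a range is assumed. Adjustment reduces the SD to 7√(1 − ρ²). The standard error (SE) is that value × √(2/194), and power comes from the noncentral t with 194 per arm.

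| ρ (assumed) | Variance cut | SE | Power |
|---|---|---|---|
| 0 (as planned) | 0% | 0.711 | 80.1% |
| 0.1 | 1% | 0.707 | 80.5% |
| 0.2 | 4% | 0.696 | 81.7% |
| 0.3 | 9% | 0.678 | 83.7% |
| 0.4 | 16% | 0.651 | 86.5% |
| 0.5 | 25% | 0.616 | 90.0% |

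**3. The same question in the planned model.** The variance of the week-24 contrast was computed by generalised least squares for a random intercept-and-slope model. Visits were weeks 0, 3, 6, 9, 12, 18 and 24, with 194 complete cases per arm. Assumptions: baseline SD 3, week-24 SD 7, residual SD 2 to 2.5.

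- Categorical time, free arm term: SE 0.711, the same as the raw difference in means. Holding the arms to a common week-0 mean reproduces the variance cuts in the table.
- Linear time, free arm term: SE 0.69 to 0.70. The common mean cuts the variance by about 4% at ρ = 0.2 and 10% to 11% at ρ = 0.3.
- If the other 65 per arm contribute a week-0 score only, the free-arm model already recovers part of the gain. With categorical time the remaining cut is about 3% at ρ = 0.2, 7% at 0.3 and 20% at 0.5.

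**4. Which correlations are plausible.** A flat distribution over 10 to 20 has an SD of about 3. The slope of week-24 on baseline PHQ-9 is then ρ × 7/3: 0.23 at ρ = 0.1, 0.47 at 0.2, 0.70 at 0.3, 0.93 at 0.4 and 1.17 at 0.5. At ρ = 0.5, one baseline point would have to predict more than one point six months later, after treatment. The lower half of the table is therefore the less likely half.

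**5. Carried imbalance.** With baseline SD 3 and 259 per arm, the chance baseline difference has SE 3 × √(2/259) = 0.26, so 95% of differences lie within about ±0.5 points. A difference of 0.5 shifts the expected unadjusted week-24 contrast by 0.5 × slope: 0.12 at ρ = 0.1, 0.23 at 0.2, 0.35 at 0.3 and 0.58 at 0.5. That is 6%, 12%, 18% and 29% of the 2-point margin.

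**6. Error control.** Simulated one-sided type I error at the margin was 0.026 without and 0.025 with adjustment at ρ = 0.3, and 0.026 for both at ρ = 0.5.

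**The case against.** The strongest reply is that nothing is broken. The unadjusted estimator is unbiased over randomizations, and its standard error already includes the variation from chance imbalance. The sample size assumed no adjustment, and the promised power is delivered. In a non-inferiority trial, lower precision makes the claim harder to reach rather than easier. All of this stands. A reader might infer from the missing adjustment that the primary test is biased, or that the trial is underpowered; the article's figures support neither inference.

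A reader might also infer that adjustment is planned only for variables found to be imbalanced. That is too strong. The sensitivity analyses also cover variables linked to dropout or missing data, which could bring in baseline PHQ-9 without any observed imbalance, and the severity moderator model contains it by construction. Neither changes the primary test.

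Finally, this is a condensed article and the analysis plan is not shown. That explains why the handling of week 0 is unstated, but the fixed effects are listed term by term. The list is a published choice, and the point holds whichever way week 0 is treated.

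**Conclusion.** The point holds as a question of efficiency and robustness, not of validity. Adjusting the primary model for baseline PHQ-9 would raise power from 80% to about 81% to 84% if the correlation is 0.1 to 0.3. It would reach 87% to 90% only at 0.4 to 0.5, which the restricted entry range makes less plausible. Adjustment would also remove a shift of roughly 0.1 to 0.35 points that a baseline difference at its 95% limit would cause at correlations of 0.1 to 0.3.

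These figures rest on SD 7, 194 completers per arm, an assumed baseline SD of about 3 and an assumed correlation. If the correlation is 0.2 or lower, the power gain is under 2 points. The recommendation is still worth making because it costs almost nothing.

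**What to change.** State one of these in the primary model, before any comparison by arm is seen:

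- **Common week-0 mean.** Keep week 0 among the outcomes, drop the arm main effect and keep arm-by-time. Participants with only a baseline score remain in the analysis.
- **Baseline as covariate.** Use post-baseline visits only as outcomes and add baseline PHQ-9, preferably with a baseline-by-time term so that its coefficient may differ by visit.

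Do the same for the WHO-5 and the PROMIS anxiety and sleep scales with their own baseline scores, assuming these are collected at the baseline assessment (the schedule figure is not readable in the text at hand). Do not rely on observed imbalance to decide whether baseline PHQ-9 is adjusted for. The sensitivity analysis for variables linked to missing data can stay as it is.

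The cost is one sentence of analysis wording. No further participants or PHQ-9 data are needed, and the sample size can stand. If the unseen analysis plan already adjusts for baseline, it is enough to record that the article's model description differs from it.

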## Study design

### Study design overview

Participants are randomly assigned in a parallel group study design to either a telehealth, synchronous group YI for individuals with depression [51] or to individual, clinician-delivered telehealth BA for depression [16]. Participant involvement lasts for 24 weeks and consists of a 12-week treatment period (i.e., either 1 weekly yoga class or 8 BA sessions over 12 weeks) and a 12-week post-treatment follow-up period. The primary outcome is depression symptom severity (assessed via the Patient Health Questionaire-9; PHQ-9) [52] at 24 weeks (i.e., 6 months). Secondary outcomes include overall well-being, anxiety symptoms, and sleep.

Participants (target N = 518) are recruited and randomized across four collaborating institutions: Massachusetts General Hospital (Boston, Massachusetts), Hennepin Healthcare Research Institute (Minneapolis, Minnesota), Butler Hospital (Providence, Rhode Island), and Wake Forest University Health Sciences (Winston-Salem, NC). The study has been approved by the Mass General Brigham Human Research Protection Program (IRB) on September 9^th^, 2022 (IRB; #2022P001701, NCT05546697). Recruitment period began on January 1^st^, 2023 and will end on May 1^st^, 2026.

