Once study staff reach participants by phone and randomize them, staff inform participants of their randomization condition (YI or BA) and provide an orientation to that intervention. Staff send out intervention-specific materials (i.e., yoga mat and orientation packet for the YI condition, or a journal, pen, and BA orientation packet for the BA condition). The participant then begins the 24-week study. Participants are automatically sent study assessments via REDCap surveys at weeks 3, 6, 9, 12, 18, and 24. In order to minimize missing data, when enrolled participants have not responded for 7 days to automated prompts to complete outcome assessments, study staff who are masked to condition reach out to these participants by phone to encourage them to complete the assessments. Participants have the option to be resent the REDCap link or to complete the surveys over the phone. Participants are compensated up to $170 for completing all study assessments. They are not compensated for intervention participation.

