As a result of this pragmatic study design, there are some key differences in the delivery of the two study interventions that may ultimately have an impact on overall participant adherence or satisfaction. First, the length of time to intervention start may differ. Because this is a study, we have made significant efforts to ensure that participants can start BA within 1–2 weeks of randomization; however, for scheduling and other reasons, this timing may not always occur. A participant can always start a yoga class in their first week after randomization. Second, another key difference in the interventions is that yoga classes are offered at 4 set times each week in a group format, whereas the BA sessions are determined based on the participant and therapist schedules, which may or may not allow for flexibility in scheduling. A third difference is that the BA participants often incur a cost per session given that most insurers require a co-pay for each BA session whereas the YI is delivered with no costs to participants. To increase accessibility of the research, we capped the out-of-pocket cost for the BA sessions at $25 out-of-pocket per session but nonetheless, the cost may be a burden to some participants. In contrast, yoga is provided at no cost to participants given that it is often not currently covered or reimbursed by insurers and to reflect that there are opportunities for free synchronous and asynchronous online classes in the community. For example, one insurer, Blue Cross Blue Shield (BCBS) of RI, offers free classes to its members at a BCBS store. Other community organizations, such as the YMCA, offer low-cost memberships which include yoga classes. A final key difference between the yoga and the BA interventions is documentation in the medical record–yoga classes are not documented in any medical record, whereas psychotherapy, or BA, must be documented to be reimbursed. As a result of these differences, study results will reflect potential outcome differences not only based on the “pure” intervention, but the interventions as they are delivered in the real-world, including several barriers to mental health treatment (i.e., access to BA) and access to potentially helpful treatments such as yoga.

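### The primary week-24 contrast is linear in time by default, with a data-dependent switch; if the arm difference bends and the line is kept, it is biased in either direction

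*Protocol article*

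**What the plan says.** The target is one time point: "The primary outcome is patient-reported depression symptom severity (PHQ-9) at week 24" (Statistical analysis). It is estimated as follows: "The difference in the mean scores at week 24 will be estimated using a linear mixed effects model with random participant intercepts and slopes". The model has "random participant intercepts and slopes and fixed effects for intervention arm, study site, time in weeks, and intervention-by-time interaction". As written, time is a single linear term, with no change of slope at week 12. The next sentence makes that form conditional: "Natural cubic splines or categorical time regression terms will be used if mean trajectories are nonlinear". Non-inferiority is then tested one-sided at 2.5% against a margin of 2 points.

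The 24 weeks fall into two parts. "Participant involvement lasts for 24 weeks and consists of a 12-week treatment period", followed by "a 12-week post-treatment follow-up period" (Study design overview). The visit times are in Study procedures: "Participants are automatically sent study assessments via REDCap surveys at weeks 3, 6, 9, 12, 18, and 24".

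The sensitivity analyses at the end of Statistical analysis add covariates to the model. None varies the form of time.

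**The concern.** A straight line is asked to cover a treatment phase and a follow-up phase, and the protocol itself gives reasons why the arm difference might bend:

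- **Start of treatment.** "A participant can always start a yoga class in their first week after randomization", whereas Design considerations allows that BA may start later. Lessons learned reports early delays of about a month.
- **After week 12.** The Behavioral activation section allows continued sessions with the study therapist where clinically needed. For yoga, the protocol describes video links and advice on other classes.

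Under a linear arm-by-time term, the week-24 difference is the end of a fitted line and not the difference observed at week 24. Where the true difference is not linear, the two diverge. In a non-inferiority trial, an estimate pulled towards zero makes a false claim easier. The switch to another form is made after the outcome means are seen, so the form of the confirmatory test is not fixed in advance. The choice also carries over to the secondary outcomes, which are analysed in the same way, and to the moderator models, which extend the primary one.

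**Working it through.** **Inputs from the protocol article.** Margin 2, one-sided 2.5%, SD 7, 25% dropout, 259 per arm, visits at weeks 3, 6, 9, 12, 18 and 24.

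**Assumptions.** The PHQ-9 is taken at every visit (the schedule figure is not shown). Baseline is part of the outcome vector (results without it are also given). The variance components, the dropout pattern and the switch rule are assumed. The difference is yoga minus BA, so positive means yoga is worse.

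**1. The plan's own figure.** n per arm = 2 × 7² × (1.96 + 0.8416)² / 2² = 192.3, so 193. The t-test version gives 194. Then 194 / 0.75 = 258.7, so 259 per arm and 518 in total. The stated sample size reproduces, and it is based on a two-group comparison at week 24.

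**2. Weights behind the linear contrast.** With complete data and a random intercept and slope on the same time term, the week-24 contrast is a fixed weighted sum of the visit differences, whatever the variance components:

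w(t) = 1/7 + (24 − m)(t − m)/S, with m = 72/7 = 10.29 and S = 1170 − 7 × 10.29² = 429.4.

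| Week | 0 | 3 | 6 | 9 | 12 | 18 | 24 |
|---|---|---|---|---|---|---|---|
| Weight | −0.19 | −0.09 | 0.01 | 0.10 | 0.20 | 0.39 | 0.58 |

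The five visits to week 12 sum to about 0.03. Weeks 18 and 24 carry 0.97.

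**3. Estimates for assumed difference curves.**

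| True arm difference | True at week 24 | Linear, baseline in | Linear, baseline out |
|---|---|---|---|
| 0 to week 12, then 1 and 2 | 2.00 | 0.39 × 1 + 0.58 × 2 = 1.55 | 1.68 |
| 0 to week 18, then 2 | 2.00 | 0.58 × 2 = 1.16 | 1.27 |
| Linear, 0 to 2 | 2.00 | 2.00 | 2.00 |
| Rises to 2 by week 12, then flat | 2.00 | 2.45 | 2.32 |
| 2 at week 12, back to 0 | 0.00 | 0.90 | 0.65 |

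**4. False non-inferiority at the margin if the line is kept.** With 194 completers per arm and SD 7 at week 24, SE² = (2/194) × [49 − σ² × (1 − 0.58)], where σ is the residual SD. For an assumed σ of 4 this gives SE = 0.66. For the ramp, the probability is Φ((2 − 1.55)/0.66 − 1.96) = Φ(−1.28) = 0.10.

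The calculation was repeated with 259 per arm, 25% dropout (spread over visits, or all early) and four sets of variance components (week-24 SD 5.2 to 6.9):

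- **Ramp after week 12:** 0.08 to 0.19.
- **Deficit only after week 18:** 0.22 to 0.50.
- **Deficit flat from week 12:** 0.001 to 0.006.

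**5. With a switch.** The switch was represented as a 5% test of the nonlinear arm-by-time terms, moving to categorical time on rejection. It detects the ramp in 38% to 67% of trials. The overall type I error is about 0.04 to 0.10 for either late-deficit shape.

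**6. Categorical time fixed in advance.** The estimate is 2.00 and the type I error 0.025 for every shape. At SD 7 with 194 per arm, SE = 7 × √(2/194) = 0.71 against 0.66 for the line. With dropout and a week-24 SD of 6.7 it is 0.65 against 0.59.

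**The case against.** The strongest reply is that the plan foresees the problem. If the means are nonlinear, it leaves the straight line, and one of its two named alternatives is the remedy proposed here. The 10% describes a model that the plan says it would then not use. The rule also speaks of mean trajectories. On a pooled-mean check (SD 7, 388 completers, assumed variance splits), a fall over 12 weeks followed by a plateau would be detected with power 0.92 to 0.96 for a 2-point fall, and at least 0.999 for 3 or 5 points. Much of this stands. The exposed case is a common trajectory that passes as linear combined with a late divergence between the arms, or a check that misses a bend in the difference.

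A reader might also infer more than the documents support:

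- **That the early visits drive the estimate.** They do not; their net weight is about 0.03.
- **That the bias always favours yoga.** It does not; a deficit that plateaus by week 12 is overstated. Nothing in the protocol predicts a loss specific to yoga. BA's eight sessions also end within 12 weeks, and yoga participants receive material for continued practice.
- **That nonlinearity is certain.** The design makes it plausible and no more.
- **That the missing trigger, knots and choice of form are the defect.** An article commonly leaves these to the SAP, which may supply them.

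What remains is what the article itself fixes: a linear default for the primary test, and a form that depends on the outcome data. A trigger written in the SAP would not change either.

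**Conclusion.** The point holds as a moderate one. The primary contrast can misstate the declared week-24 difference if the arm difference is nonlinear and the linear form survives the check. In the assumed examples, a true difference at the margin is estimated as 1.55 or as 2.45, depending on shape. False non-inferiority for the late ramp is about 10% (0.08 to 0.19) if the line is kept, and about 0.04 to 0.10 for late deficits if a 5% test on the arm difference acts as the switch.

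The weights in step 2 follow from the visit schedule alone, given complete data and baseline in the model. The error rates rest on assumed curves, variance components, dropout pattern and switch rule. They show what can happen and are not a forecast for this trial. It would be wrong to read 10% as the trial's type I error, because that figure requires both a late bend in the difference and retention of the line. Curvature common to both arms does not bias the contrast with complete data. The sample size is not in question.

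**What to change.** Before outcome data by arm are examined, state that the primary model uses categorical assessment time (weeks 0, 3, 6, 9, 12, 18 and 24) with arm-by-visit terms, and that the week-24 contrast comes from it. Delete the conditional sentence for the primary analysis and keep linear or spline fits as supportive. The within-participant covariance can be left to the trial statistician; unstructured is one option. Apply the same form to the secondary outcomes.

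The change is one of wording. The price is a standard error about 7% to 10% larger than that of a correctly specified linear model (0.71 against 0.66; 0.65 against 0.59). Across all the variance and dropout settings tried, the increase was about 3% (0.68 against 0.66) to 13% (0.51 against 0.45). No additional participants are needed, because the 518 was already derived from a two-group comparison at week 24.
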